#### Measures taken to avoid bias

All necessary steps will be taken to reduce the risk of bias.^28 29^ The trial will be analysed on an intention-to-treat basis, that is, outcomes will be analysed according to the treatment allocation, irrespective of future management and events, and every effort will be made to include all randomised patients. Selection bias will be minimised by concealed randomised allocation. Patients, clinicians and researchers will be blinded to the intervention to minimise procedural bias. Detection bias will be minimised by objective source data verification of the data for the primary endpoint and blinding of laboratory staff analysing biomarkers and inflammatory processes. Detection bias for clinical outcomes that are not part of the primary endpoint will be minimised using objective outcome criteria; as defined in the outcome section above and recorded in a blinded manner. Decisions about discharge from ICU, HDU and from hospital will be made by clinical staff based on existing institutional protocols. ICU/HDU transition will be defined as transition from level 3 (1:1 nursing ratio) to level 2 (1:2 nursing ratio). HDU/ward transition will be defined as time of arrival on the ward. To minimise attrition bias, we aim to include data for all randomised participants in the data analyses.

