### Statistical analyses

The primary outcome for the trial will be the serum creatinine values measured postoperatively, adjusted for baseline values. On the basis that observed SD for serum creatinine values from the MARACAS trial was 37 μmol/L, and the mean observed correlation between baseline and six postsurgery measures was 0.84, we estimate that a sample size of 56 patients per group will have a 90% power to detect a mean difference of 10 μmol/L for serum creatinine values over six postintervention time points, between treatment and control groups with an alpha value of 0.05. This equates to a moderate effect size. Additionally, the study has 80% power to detect a 33% reduction in the frequency of AKI, as a secondary endpoint. We propose to recruit 126 patients (63 per group) anticipating that 10% of patients will be treated outside of the protocol, withdrawn or lost to follow-up.

AKI is a key secondary endpoint of interest. If the observed KDIGO AKI event rate was 65%, as observed in the MARACAS trial, a sample size of 59 patients per group will allow us to detect an absolute reduction in the frequency of AKI to 40% with an 80% power and 5% significance (two-tailed).

Specific morbidities and other adverse events are too infrequent for the trial to be able to detect differences between the treatment and control groups. Frequencies of these adverse outcomes will be tabulated, in line with guidelines for reporting adverse events in trials.^29^ Our mechanism substudy will be performed on a subgroup of 96 patients. As this analysis is exploratory, no power calculation was performed.

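### The 10% recruitment allowance counts off-protocol patients as lost although intention to treat keeps them; AKI power at 63 per group is about 74–79%, not 80%, and the primary 90% is at risk only conditionally

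*Protocol article*

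**What the plan says.** All the sample-size figures are in the protocol article under Statistical analyses.

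- **Primary outcome:** "a sample size of 56 patients per group will have a 90% power to detect a mean difference of 10 μmol/L". The variability input is "observed SD for serum creatinine values from the MARACAS trial was 37 μmol/L". For baseline adjustment, the plan relies on a single figure: "the mean observed correlation between baseline and six postsurgery measures was 0.84".
- **AKI, called a key secondary endpoint:** with a 65% rate in controls, "a sample size of 59 patients per group will allow us to detect an absolute reduction in the frequency of AKI to 40" per cent, with 80% power at a two-tailed 5% level.
- **Recruitment:** 126 patients, 63 per group, "anticipating that 10% of patients will be treated outside of the protocol, withdrawn or lost to follow-up". The split of the 10% among these three groups is not given.

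Measures taken to avoid bias defines intention to treat: "outcomes will be analysed according to the treatment allocation, irrespective of future management and events". Plan of analysis makes this the basis of the primary analysis. Wrongly treated or incompletely compliant patients are removed only in the per-protocol comparison under Sensitivity analysis. The Sildenafil section counts as a deviation both not giving the allocated drug and giving it otherwise than the protocol specifies.

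**The concern.** Dividing by 0.9 is the correction for patients who contribute no outcome. It suits those withdrawn or lost, and it would suit a per-protocol analysis set. It does not suit patients treated off protocol, whom the primary analysis retains in their allocated arm. A retained sildenafil patient who had little or no drug leaves the sample size intact but shrinks the average difference between arms. For a share c with no effect at all, the required inflation is close to 1/(1−c)² and not 1/(1−c).

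A second, separate gap concerns AKI. The 10% was applied to the 56 for the primary outcome but not to the 59 for AKI, so the recruitment target does not cover the plan's own allowance for that endpoint.

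What is at stake is how the results are read. A null AKI result would be credited with 80% power that the plan's own figures do not support.

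**Working it through.** **Inputs from Statistical analyses:** SD 37 μmol/L; baseline correlation 0.84; six post-surgery measures; difference 10 μmol/L; 56 per group for 90%; AKI 65% versus 40%, 59 per group for 80%; 63 recruited per group; 10% allowance. **Assumptions not in the documents:** two-sided alpha for the primary outcome, the correlation among post-surgery values, the split of the 10%, and the effect left in deviators.

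**Reproducing the plan's figures**

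- Inflation: 56/0.9 = 62.2, so 63. Exact.
- AKI, unpooled formula: n = (1.960 + 0.842)² × (0.65×0.35 + 0.40×0.60)/0.25² = 58.7, so 59. Exact. The pooled formula gives 62.
- Primary, mean change from baseline with every correlation 0.84: SD = 37 × √[(1 + 5×0.84)/6 + 1 − 2×0.84] = 15.99, and n = 2 × (15.99 × 3.2415/10)² = 53.7, so 54. This is within 2 of 56.
- Primary, baseline-adjusted with every correlation 0.84: SD = 37 × √[(1 + 5×0.84)/6 − 0.84²] = 14.85, so 47 per group. It gives 56 if the correlation among post-surgery values is about 0.88.

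As the variance behind 56 is not fully stated, I calibrated it so that 56 per group gives exactly 90%: SD = 10/(3.2415 × √(2/56)) = 16.32.

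**Power at 63 recruited per group**

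Let l be the share lost and c the share kept as deviators, with l + c = 0.10. Then n = 63(1−l). If deviators in the sildenafil arm have no effect, the average effect is multiplied by 1 − c/(1−l).

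- Primary: Φ(Δ/(16.32 × √(2/n)) − 1.96), with Δ equal to 10 times that factor.
- AKI, unpooled: Φ(d/√([p₁(1−p₁) + p₂(1−p₂)]/n) − 1.96), with p₁ = 0.65, d equal to 0.25 times the factor, and p₂ = 0.65 − d.
- AKI, pooled: Φ((d√n − 1.96√[2p̄(1−p̄)])/√[p₁(1−p₁) + p₂(1−p₂)]), where p̄ is the mean of p₁ and p₂.

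| Make-up of the 10% | n per group | Effect factor | Primary | AKI, unpooled | AKI, pooled |
|---|---|---|---|---|---|
| All lost | 56.7 | 1 | 90.3% | 78.6% | 76.7% |
| 5% lost, 5% kept, no effect | 59.85 | 0.947 | 88.8% | 76.2% | 74.4% |
| All kept, no effect | 63 | 0.90 | 87.2% | 73.9% | 72.2% |
| All kept, half the effect | 63 | 0.95 | 90.4% | 78.5% | 76.8% |

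**Separating the two causes for AKI.** With all 63 analysed at full effect, unpooled power is 82.7%. Pure loss of 10% takes it to 78.6%, solely because 59 was not inflated; covering that would need 59/0.9 = 65.6, so 66 per group. Dilution accounts for the further fall to 76.2% or 73.9%.

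**Sensitivity of the primary figure to the variance**

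- Change-score SD 15.99: 91.5% (all lost), 90.0% (5%/5% split), 88.5% (all kept, no effect).
- Baseline-adjusted, all correlations 0.84: 94.8% (all lost) to 92.5% (all kept, no effect).

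**The case against.** A reader might infer that 63 per group fails to deliver the stated 90% on the primary outcome. The documents do not support that as a flat statement.

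- It needs an unstated split of the 10% and little or no effect in deviators. The protocol's definition of a deviation includes patients who received some sildenafil. If deviators keep half the effect, primary power is 90.4%, so dilution does not always cost more than loss.
- The 0.88 correlation that leaves no slack is solved for, not stated. With 0.84 throughout and baseline adjustment, power never falls below 92%. The 0.84 is equally an assumption, so the question stays open.
- Placebo patients who deviate without receiving sildenafil cause no dilution. Crossover of the full 10% in both arms would lower primary power to 78.5%, but nothing in the documents suggests it.

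These points stand, and they limit the primary claim to a conditional one.

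It can also be said that AKI did not set the sample size, that the AKI gap under pure loss is under 2 points with the unpooled formula, and that an article may leave the split of an attrition allowance to a fuller document. The first two are true and keep the matter minor. The third does not remove the mismatch: the article itself places off-protocol patients in a loss correction and also keeps them in the analysis. Nor is this an arithmetic slip, since 63 is the correct result of the division. The fault lies in which patients the division is applied to.

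**Conclusion.** The point holds in a limited form and is minor. The inflation rule does not match the intention-to-treat set.

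For AKI (65% versus 40%), the stated 80% is missed in every case examined that uses the full 10% as loss, or as retention with half or no effect: about 74–79% unpooled and 72–77% pooled. It would be met (unpooled) with no dilution if loss stayed within 4 of 63 (6.3%), leaving 59. It would also be met if all 10% were retained with about two thirds of the effect or more: d = 0.2417 gives 80.0%, and 0.2417/0.25 = 0.967 = 1 − 0.10 × (1 − 0.67).

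For the primary outcome, a shortfall is possible but not shown. Under the 56-per-group calibration, it is about 1 point below 90% for a 5%/5% split and about 3 points if all 10% are kept with no effect in the sildenafil arm.

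**What to change.** Keep 126 patients as the target and change the wording under Statistical analyses:

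1. State the assumed split of the 10% between missing outcome data and protocol deviation.
2. Use n/(1−d) for missing data only, with d the share missing. For retained deviators, use a reduced effect and say how much effect is assumed to remain.
3. Restate AKI power for 65% versus 40% at 63 recruited per group as about 74–79% instead of 80%, naming the variance formula.
4. Give the primary power as 90% conditional on the stated assumptions, with about 87% as the worst case under the 56-per-group calibration, and state the correlation assumed among post-surgery values.

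The cost is wording and a slightly less favourable stated power, with no extra patients. Guaranteeing 80% for AKI would be a different decision, with a larger trial: 66 per group for pure loss, or 59 replaced by about 74 (unpooled) if all 10% are kept with no effect. This is not requested, because the primary outcome sets the size.

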#### Plan of analysis

The primary analysis will take place when follow-up is complete for all patients and will be performed on an intention-to-treat basis. Continuous longitudinal outcomes will be compared using linear mixed-effects methodology with the treatment group and study design variables fitted as fixed effects, and patient terms as random effects. Binary outcomes will be compared between treatment groups using logistic regression. Continuous outcomes will be compared using linear regression. Time to event outcomes will be compared using Cox’s proportional hazards models. All statistics will be reported with 95% CIs.

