Estimate the difference in serum creatinine levels (measured daily for up to 7 days postoperatively and adjusted for baseline values) between patients allocated to the sildenafil and placebo groups.Estimate the difference in the frequency of AKI (defined as a rise in serum creatinine of >26 µmol/L within 48 hours or a doubling of the serum creatinine within 7 days as defined by the KDIGO criteria)^4^ between patients allocated to the sildenafil and placebo groups. Individuals who receive renal replacement therapy (RRT), including haemofiltration, are considered to have met the criteria for stage 3 AKI irrespective of the stage they are in at the time of RRT.Estimate the difference in biomarkers of postoperative renal injury, and myocardial injury, between patients allocated to the sildenafil and placebo groups.Estimate the difference in the frequency of sepsis, low cardiac output, acute lung, brain or gut injury or death between patients allocated to the sildenafil and placebo groups. These outcomes, along with the primary outcome will also be considered as a composite endpoint.Estimate the difference in Multiple Organ Dysfunction Scores between patients allocated to the sildenafil and placebo groups.Estimate the difference in the frequency of other adverse events not listed above between patients allocated to the sildenafil and placebo groups.Estimate the median difference in hospital length of stay between patients allocated to the sildenafil and placebo groups.Estimate whether sildenafil increases the frequency of adverse drug reactions; specifically hypotension that requires treatment or allergic responses.Estimate whether the observed effects of sildenafil may be attributable to changes in endothelial function.Estimate whether the observed effects of sildenafil may be attributable to changes in platelet, leucocyte or endothelial cell activation.

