#### Randomisation and code breaking

Patients will be randomly assigned in a 1:1 ratio to either sildenafil or placebo using an internet-based randomisation system (Sealed Envelope, MHRA recognised facility), which will be managed by Leicester Clinical Trials Unit (LCTU). Randomisation will be stratified by (1) type of procedure: coronary artery bypass grafting (CABG), valve, CABG and valve, other; and (b) baseline eGFR: <60, ≥60. Random allocations will be generated only after the relevant baseline data to identify the patient has been entered into the system, guaranteeing concealment of allocation and a definitive log of participants. Patients who consent will be randomised by the unblinded member of the research team. If patients are unexpectedly rescheduled, they will retain their trial numbers and randomised allocation. Detailed instructions for the randomisation process will be provided in a separate manual (figure 1).

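### The named models do not deliver the median difference in hospital stay, and no step is stated from the logistic model to the difference in AKI frequency that the objectives and sizing use

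*Protocol article*

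**What the plan says.** Two objectives in Aims and objectives name a quantity. For AKI: "Estimate the difference in the frequency of AKI" between the groups. For stay: "Estimate the median difference in hospital length of stay between patients allocated to the sildenafil and placebo groups".

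Statistical analyses treats AKI as the key secondary endpoint and sizes it on an absolute reduction from 65% to 40%, with 59 per group, 80% power and a two-sided 5% level.

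Plan of analysis gives one sentence per outcome type:

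- Repeated continuous outcomes: "linear mixed-effects methodology with the treatment group and study design variables fitted as fixed effects", with patient terms as random effects.
- Binary outcomes, then single continuous outcomes: "Binary outcomes will be compared between treatment groups using logistic regression. Continuous outcomes will be compared using linear regression".
- Times to event: "Time to event outcomes will be compared using Cox’s proportional hazards models".

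It asks for 95% CIs throughout. It does not assign length of stay to any of these models, and it names no effect measure for any of them. On allocation, Randomisation and code breaking states: "Randomisation will be stratified by (1) type of procedure", and adds baseline eGFR below 60 or not as a second factor. Table 2 shows urine NGAL and RH-PAT each measured once before surgery and once on day 1.

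**The concern.** An objective that names a quantity should be met by an analysis that estimates it. For stay, the objective is a difference in medians and the listed methods target other quantities. For AKI, the objective and the sample size are on the absolute scale, while the only named method has the odds ratio as its usual output.

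Two things are at stake. First, AKI is expected in well over half of control patients, and at that frequency an odds ratio is far from a risk ratio and is easily misread as one. Second, if the plan leaves the scale open, it can be chosen after the results are known. For stay, which is usually skewed, a mean difference and a median difference can differ appreciably, and a hazard ratio is not in days at all.

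**Working it through.** **1. The plan's own AKI figure.** Inputs from Statistical analyses: 65%, 40%, 80% power, two-sided 5%. The unpooled risk-difference formula gives

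n = (1.95996 + 0.84162)² × (0.65×0.35 + 0.40×0.60) / 0.25² = 7.849 × 0.4675 / 0.0625 = 58.7, so 59 per group.

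This matches the stated 59, so the sizing is consistent with a comparison of absolute risks.

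**2. The same effect on three scales.**

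- Odds ratio: (0.40/0.60) / (0.65/0.35) = 0.36
- Risk ratio: 0.40/0.65 = 0.62
- Risk difference: 0.40 - 0.65 = -25 points

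With 59 per group and these rates observed:

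- Risk difference: SE = √(0.4675/59) = 0.089, so the reduction is 25 points (95% CI 7.6 to 42.4).
- Odds ratio: SE of the log = √[1/(59×0.2275) + 1/(59×0.24)] = 0.381, so 0.36 (95% CI 0.17 to 0.76).

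Read as a risk ratio, 0.36 suggests a 64% reduction; the relative risk reduction is 25/65 = 38%.

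**3. The odds ratio alone does not fix the risk difference.** Holding it at 0.359, treated odds = 0.359 × control odds:

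| Control risk | Treated risk | Risk difference (points) |
|---|---|---|
| 30% | 13.3% | -16.7 |
| 50% | 26.4% | -23.6 |
| 65% | 40.0% | -25.0 |
| 80% | 58.9% | -21.1 |

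**4. Length of stay.** The article gives no distribution, so this is an illustration. Assume log-normal stays with medians of 10 and 8 days and the same log-SD s in both groups. The mean is the median × exp(s²/2), so the mean difference is 2 × exp(s²/2):

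| s | Median difference (days) | Mean difference (days) |
|---|---|---|
| 0.5 | 2.0 | 2.3 |
| 0.8 | 2.0 | 2.8 |
| 1.0 | 2.0 | 3.3 |

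**5. Covariates: what they could add.** All inputs here are assumed.

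- Adjusting a single postoperative value for a baseline with correlation r multiplies residual variance by 1 - r². At r = 0.3, 0.5 and 0.7 this is 0.91, 0.75 and 0.51, giving CI widths of 95%, 87% and 71% of the unadjusted width.
- Under simulation with 56 per group and two equal strata balanced by design, an unadjusted nominal 5% comparison of means rejected a true null in about 4.3%, 3.0% and 0.4% of trials when strata differed by 0.5, 1 and 2 SD.
- Unadjusted logistic regression rejected in about 3.9% for stratum risks of 50% and 80%, and 2.0% for 40% and 90%.

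Omitting the strata is therefore conservative.

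**The case against.** **AKI.** A difference in frequency can be ordinary language for any between-group comparison; the article uses the same phrase for sepsis, death and other adverse events. Logistic regression is a valid test of 65% against 40% and can yield a risk difference. The article does not say that only odds ratios will be reported, and the choice of scale may sit in an analysis plan that is not shown. Most of this stands: the method is not wrong. What remains is that the sizing is explicitly absolute and nothing stated carries the analysis back to that scale.

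**Stay.** It is one secondary outcome, no model is assigned to it, and medians could be derived from a fitted Cox model. That would be an extra, unstated step, so the mismatch with the objective remains.

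**Covariates.** A reader might infer that the logistic, linear and Cox models leave out the stratification factors and baseline values. The article does not support that. It is silent on covariates for these models, and silence is not exclusion; covariate lists are commonly left to the analysis plan or full protocol. Where it does give detail, design variables are included. Outcomes with several postoperative values, such as MODS, troponin and flow cytometry, would fall under the mixed model. The article gives no AKI rate by eGFR stratum and no biomarker correlation, so the size of any gain is unknown.

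**Power.** A reader might also infer that the trial is undersized because the log-odds-ratio formula gives 7.849 × (1/0.2275 + 1/0.24) / 1.0245² = 64.03, or 65 per group. That is one of several approximations to the same comparison (the pooled formula gives 62) and does not make the stated 59 wrong.

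**Conclusion.** The mismatch holds, and most clearly for length of stay: the objective is a median difference and none of the named models directly estimates one. It holds more mildly for AKI, where the analysis is valid but the scale used in the objective and the sizing is not the scale the named model reports by default. At the planning rates the gap is an odds ratio of 0.36 against a risk ratio of 0.62 and a difference of -25 points. These AKI figures rest only on the article's own rates; the stay figures rest on assumed medians and a log-normal shape.

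The covariate element is a suggestion, not an error. Leaving the factors out would cost precision by an amount that rests on assumed correlations and stratum effects, and would not inflate false positives. The primary outcome is unaffected: it is already adjusted for baseline, with design variables fitted.

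**What to change.** 1. **Length of stay.** Name a method that estimates the median difference with 95% CI, for example quantile regression, and state how in-hospital deaths are handled (ranking them as the longest stay is one option).
2. **AKI.** Keep the logistic model. Report the risk difference standardised from it, with 95% CI, alongside the odds ratio.
3. **Optional, for precision.** Extend the design variables already named for the mixed model (procedure type and eGFR stratum) to the AKI logistic model, and include the preoperative value for outcomes with a single postoperative measure (urine NGAL, RH-PAT).

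The cost is a few sentences in the analysis plan and standard code, settled before unblinding. No new data, extra patients or change in conduct are needed.

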#### Sensitivity analysis

Two sensitivity analyses are planned, comparing effect estimates for the primary outcome for (1) a per-protocol comparison including only those patients who receive the allocated intervention, that is, excluding patients who receive the incorrect intervention, are withdrawn prior to the intervention, or where there is incomplete compliance with intervention, (2) including only patients with complete follow-up data.

### Trial management

The trial will be managed by the Cardiac Surgery Clinical Trials Team at the University of Leicester, supported by the LCTU, a UK Clinical Research Collaboration registered CTU. The CTU will manage an internet-based randomisation system. They will develop and maintain the trial database, check data quality as the trial progresses and carry out statistical analyses in collaboration with the clinical investigators.

